## Abstract

**Introduction:** Quantitative sensory testing is frequently used in research to assess endogenous pain modulation mechanisms, such as Temporal Summation (TS) and Conditioned Pain Modulation (CPM), reflecting excitatory and inhibitory mechanisms, respectively. Numerous studies found that a dysregulation of these mechanisms is associated with chronic pain conditions. In turn, such a patient's “profile” (increased TS and/or weakened CPM) could be used to recommend different pharmacological treatments. However, the procedure to evaluate these mechanisms is time-consuming and requires expensive equipment that is not available in the clinical setting. In this study, we aim to identify psychological, physiological and socio-demographic markers that could serve as proxies to allow healthcare professionals to identify these pain phenotypes in clinic, and consequently optimize pharmacological treatments.

**Method:** We aim to recruit a healthy participant cohort (*n* = 360) and a chronic pain patient cohort (*n* = 108). Independent variables will include psychological questionnaires, pain measurements, physiological measures and sociodemographic characteristics. Dependent variables will include TS and CPM, which will be measured using quantitative sensory testing in a single session. We will evaluate one prediction model and two validation models (for healthy and chronic pain participants) using multiple regression analysis between TS/CPM and our independent variables. The significance thresholds will be set at *p* = 0.05, respectively.

**Perspectives:** This study will allow us to develop a predictive model to compute the pain modulation profile of individual patients based on their biopsychosocial characteristics. The development of the predictive model is the first step toward the overarching goal of providing clinicians with a set of quick and cheap tests, easily applicable in clinical practice to orient pharmacological treatments.

## Introduction

Chronic pain, which affects one in five people worldwide (1), has been defined as pain that persists beyond the usual healing time (2). However, merely relying on this temporal aspect is not enough to account for the complexity of chronic pain vs. acute pain. As such, the notion of inadequate response to treatment and significant, lasting alterations of functional and psychosocial status have increasingly been recognized as an integral part of this condition (3). Several factors have been associated with chronic pain, including physical limitations (4, 5), cognitive impairments (6), and psychological conditions, such as anxiety and depression (7).

Dysregulations of endogenous pain modulating systems are also thought to be involved in the development of chronic pain. These dysregulations include increases in pain facilitation [which amplify our body's alertness (8)], and decreases in pain inhibition [which triggers diffuse hypoalgesia (9)]. These endogenous pain modulation mechanisms can be measured using quantitative sensory testing based on Temporal Summation (TS) and Conditioned Pain Modulation (CPM), respectively. Both of these testing paradigms have high test-retest reliability (10–12).

TS is the psychophysical correlate of central sensitization, which is defined as an increased responsiveness of second order neurons (located in the spinal cord) to afferent C-fibers (13) resulting in a heightened pain perception (14). Increased TS is thought to be involved in various chronic pain conditions, such as fibromyalgia (14, 15), chronic low back pain (16), and painful knee osteoarthritis (17). CPM, on the other hand, refers to the phenomenon wherein a noxious stimulation results in widespread hypoalgesia (18), akin to the diffuse noxious inhibitory control involving a spino-bulbo-spinal loop studied in animal models (9, 19). Weakened CPM is found in chronic pain conditions, such as chronic tension headaches (20), provoked vestibulodynia (21), atypical trigeminal neuralgia (22), temporomandibular disorders (23), fibromyalgia (24), and irritable bowel syndrome (23).

TS and CPM measures can be used to identify individuals at risk of developing chronic pain (25). For example, the amplitude of pre-operative TS is correlated with the intensity of post-operative pain (26), while a placebo-controlled study has found that weaker CPM is associated with a better response to duloxetine (a serotonin-noradrenalin reuptake inhibitor) in patients suffering from neuropathic pain (27). This line of research has led authors to suggest that it is the presence of specific deficits in endogenous pain modulation mechanisms, rather than the type of chronic pain, that best predicts response to treatment (28, 29). Indeed, according to Yarnitsky and colleagues, each individual can be placed along a spectrum ranging from an *anti*nociceptive (normal TS/effective CPM) to a *pro*nociceptive (increased TS/weak CPM) profile, and as such should be more receptive to an individually tailored treatment that specifically counteracts their deficits (25).

The evaluation of these endogenous mechanisms could therefore prove useful in the clinic, by providing healthcare professionals with valuable information regarding the pain modulation profile of patients to help them choose the most appropriate pharmacological approach. Unfortunately, to the best of our knowledge, no study has attempted to estimate the amplitude of TS and CPM using readily accessible measures. Protocols currently used to evaluate endogenous pain modulation mechanisms are time consuming and require expensive, complex equipment that would not be practical for daily clinical practice. As such, an alternative approach, which would allow clinicians to easily estimate their patient's CPM and TS using readily available tests, would be highly relevant to clinical practice.

Despite the lack of predictive models using TS and CPM as outcome, numerous association studies suggest that certain factors influence endogenous mechanisms. TS and CPM have long been known to be affected by age and sex (30–38), but more recently they have also been linked to a number of other psychophysiological variables. For instance, TS is consistently associated with pain catastrophizing (39–42), whereas CPM is modulated by both catastrophizing (43, 44) and expectations (45); additionally, a wide array of other psychological factors have been related to pain mechanisms, albeit in a method-dependent manner [for a review, see (46)]. Certain physiological factors, such as blood pressure, also seem to correlate with TS/CPM (47, 48) response, whereas others, such as activation of endocannabinoid and opioid systems, are known to directly contribute to pain inhibition (49–51). Moreover, a lower plasma concentration of dopamine (52) and catecholamines (norepinephrine and serotonin) (53) is associated with deficient CPM in chronic pain patients and, interestingly, it seems that this low plasma concentration is attributable to genetic polymorphisms, which suggests that CPM deficiency could in fact have a genetic correlate (54).

Different approaches have been developed (based on similar theoretical frameworks) to assess endogenous mechanisms. For TS, constant (47, 53–55) and pulsed (15, 31, 56, 57) nociceptive stimulations are commonly used, with a large variety of stimuli (58). For CPM, protocols include parallel (27, 34, 59, 60) or sequential (35, 38, 61–63) paradigms. In this context, the heterogeneity of the aforementioned studies and approaches makes it difficult to draw any meaningful generalization (64). Moreover, these factors have yet to be systematically evaluated within a single study.

The first objective of this study is to develop and validate a predictive model to estimate the amplitude of TS and CPM. Our second objective is to estimate reference values of these endogenous excitatory and inhibitory modulation mechanisms of pain in a healthy population.

## Methods

### Participants

Our participants will take part in a single experimental session, taking place at the Centre de Recherche du CHUS (Sherbrooke, Quebec, Canada). Eligibility criteria (56) are listed in Table 1. We will ask that participants refrain from consuming tobacco (65, 66), alcohol (67, 68), and stimulants (69) (caffeine, theine, etc.) in the 24 h preceding the experimental visit, and that they skip their last dose of pain medication (acetaminophen, non-steroidal anti-inflammatory drugs, and narcotics), such that they are not under the influence of an analgesic agent during the session. Recreational substances are also prohibited up to 7 days before the testing. Participants who fail to adhere to these instructions will be asked to reschedule their session. Participants will be recruited using volunteer registers; Facebook advertisement, posters, and leaflets; those interested will be invited to contact the team and to complete screening questionnaires to confirm their eligibility.

**Table 1 T1:** Eligibility criteria.

	**Chronic pain patients**	**Healthy Participants**
Inclusion criteria	Able to understand instructions	
	18–79 years of age	
	Chronic Pain condition (>6 months)	Free from chronic pain condition
Exclusion criteria	Chronic headache	
	Pregnancy, or post-partum (<1 year) status	
	Active cancer or cancer-related pain	
	Cardiac or vascular diseases	
	History of psychotic or neurocognitive disorder	
	Regular use of recreational substances	
	Acute or chronic arm injury, including impaired sensitivity	

### Independent Variables

#### Psychological Distress

A number of psychological conditions are comorbidities of chronic pain (7). For this reason, different psychological variables will be evaluated.

##### Anxiety and Depression

The *Hospital Anxiety and Depression Scale* is an instrument used to screen for anxiety and depressive disorders. It comprises 14 items (seven each for anxiety and depression) rated from 0 to 3, for a maximum score of 21. Subjects are classified as presenting no symptoms (≤7), mild symptoms (8–10), or moderate to severe symptoms (≥11) for both disorders. The psychometric properties of this questionnaire are qualified as excellent (70).

##### Catastrophizing

The *Pain Catastrophizing Scale* (71) is a 13-item questionnaire representing the three components of pain catastrophizing: rumination, magnification, and helplessness. A score above 30/52 indicates a clinically significant level of catastrophizing. This questionnaire has good psychometric properties (72).

#### Pain Measurements

##### Pain Intensity

The *Brief Pain Inventory (BPI)* (73) will be used to measure pain intensity and interference with daily life. The BPI is a generic, self-administered pain questionnaire for chronic pain conditions. The psychometric qualities of this test are excellent (74–76).

##### Pain Type

The *Douleur Neuropathique 4* (77) is a diagnostic tool used to identify neuropathic pain. It assesses pain symptoms (type of pain and presence of dysesthesia, out of seven) and signs (physical examination, out of three). A score ≥ 4/10 suggests a neuropathic component. This tool is regularly used in research, and has excellent psychometric properties (77).

##### General Clinical Pain

A pain diary will be used to measure daily clinical pain. Participants with chronic pain will be asked to indicate the highest, average and lowest level of pain they feel on seven occasions (3 days prior to the visit, the day of the visit and the 3 days following the visit).

##### Somatization

The *Somatization* subscale of the *Symptoms Checklist 90* (78, 79) will be used to assess somatization in our participants. The subscale comprises 12 items, each rated on a 5-point scale. Psychometric properties of this subscale are excellent (79).

##### Mechanical Pain Threshold

A digital algometer will be used to assess the mechanical pain threshold (i.e., the point at which a mechanical pressure starts to elicit pain). The algometer will be placed on the upper trapezius muscle, and the pressure will be gradually increased until the participant verbally reports pain. Four trials will be conducted—two on each side—and the average pressure required to reach the mechanical pain threshold will be recorded. This test has good to excellent reliability and validity (80–82).

##### Pain Persistence

A digital algometer will be used to assess pain persistence. Following the mechanical pain trials described above, the algometer will be applied on the right upper trapezius muscle, and pressure will be increased until participants verbally report a pain intensity of 5/10 (numerical rating scale). This pressure will be maintained for 20 s (Tonic Mechanical Pain test). Immediately after the algometer is removed, participants will be asked to rate the intensity of their lingering pain sensation (if any), again using the numerical rating scale. Pain scores will subsequently be collected every 2 min, until participants report two consecutive scores of 0/10.

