### Procedure

At the beginning of the session, we will reassess participants' eligibility, and we will collect their informed consent. We will also collect data relating to our independent variables, using a series of questionnaires, physiological measures, and a blood sample. All questionnaires will be provided in each participant's preferred language (English or French). We will then assess the amplitude of their CPM and TS using quantitative sensory testing (Figure 1):

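### The pain-persistence ratings stop only at two consecutive 0/10 scores, with no maximum and no rating at the site beforehand, so the score may be arbitrary or missing mainly in chronic pain participants

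*Protocol article*

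**What the plan says.** The Pain Persistence section of the protocol article comes under Independent Variables. After the mechanical threshold trials, "the algometer will be applied on the right upper trapezius muscle", the pressure is raised until the participant reports 5/10, and it is held for 20 s. On release, "participants will be asked to rate the intensity of their lingering pain sensation (if any". The end rule follows: "Pain scores will subsequently be collected every 2 min, until participants report two consecutive scores of 0/10". The section describes no rating at the site before the pressure and no largest number of ratings. It does not say which summary of the scores becomes the predictor.

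The Participants section and Table 1 say who takes the test. Patients enter with "Chronic Pain condition (>6 months", with no restriction on body site. The exclusions tied to a pain location are chronic headache, cancer-related pain and "Acute or chronic arm injury, including impaired sensitivity". Participants skip their last dose of pain medication, "such that they are not under the influence of an analgesic agent during the session". All measurements fall in one visit: "Our participants will take part in a single experimental session".

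The Procedure section describes collecting the independent variables and continues: "We will then assess the amplitude of their CPM and TS using quantitative sensory testing (Figure 1". Figure 1, which shows the sequence, is not available in the text reviewed.

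**The concern.** A return to 0/10 is a natural end point for someone who starts at 0/10. It is not one for a patient whose trapezius already hurts at rest, and such patients are eligible. Without a rating beforehand, neither the patient nor the assessor has a reference for separating evoked pain from pain that was already there. The rule also gives staff no stated way to end the test in a participant whose after-sensation lasts very long, which is the response the test is meant to detect.

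What is at stake is the meaning of one candidate predictor. If the score is a time to zero or a summary of the whole curve, its value in these patients depends on when staff decide to stop, or does not exist. Lasso selection and the mean square prediction error both need a number for each participant. The Statistical Analyses section also compares prediction error between the healthy and chronic pain validation cohorts. A predictor that measures after-sensation in one cohort and partly background pain in the other weakens that comparison.

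**Working it through.** The documents give no figure for the length of this test or for the share of patients with pain at the trapezius, so there is no stated figure to reproduce. The check sets the rule against eligibility and then shows a range.

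**Step 1: can the rule fail to end?** Assume the first rating comes at 0 min and the rest every 2 min. If k non-zero ratings precede the two zeros, the test ends at 2 × (k + 1) min.

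| Non-zero ratings k | End of test (min) |
|---|---|
| 0 | 2 |
| 5 | 12 |
| 10 | 22 |
| 15 | 32 |
| 30 | 62 |

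If the score never reaches 0, no end time is defined.

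**Step 2: can eligible participants be in that position?** The test site is the right upper trapezius. Table 1 excludes arm injury and chronic headache but not neck, shoulder or widespread pain. The Introduction names fibromyalgia among the conditions of interest. Resting pain at the test site is therefore compatible with eligibility.

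**Step 3: how many?** The Sample Size section gives 54 patients in the discovery cohort of 360 (54 / 360 = 15%) and 54 in the chronic pain validation cohort, so 54 + 54 = 108. Let q be the share with constant pain at the trapezius. The documents do not give q; the range of 5% to 30% is an assumption.

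- q = 5%: 54 × 0.05 = 2.7, about 3 patients in each cohort, or 2.7 / 360 = 0.75% of the discovery cohort.
- q = 30%: 54 × 0.30 = 16.2, about 16 patients in each cohort, or 16.2 / 360 = 4.5% of the discovery cohort.
- Chance of at least one such patient among 54 at q = 5%: 1 − 0.95^54 = 0.94.

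These are patients who may not meet the rule. Some will separate the two pains and report 0/10.

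**Step 4: which summaries are exposed?** The stopping rule affects time to zero and any area or curve summary. It does not affect the first score after release, which every participant has, although without a baseline that score may also include resting pain.

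**Step 5: does it reach the outcomes?** Under TS and CPM Amplitude, TS uses only the first heat stimulus. Under Post-CS Test Stimuli, the second heat stimulus follows the cold bath immediately. Nothing in the text places the persistence test between the first heat stimulus and the cold bath. The persistence test does follow the threshold trials, and Pre-CS Test Stimuli refers back to that threshold. If those same trials supply the pre-conditioning value, a long persistence test would widen the gap before the post-conditioning threshold, but only for mechanical CPM.

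**The case against.** The strongest reply rests on wording. The first rating concerns the lingering sensation, if any, and the later scores are described as following on from it. In a section on pain persistence, the natural reading is that evoked pain alone is rated throughout. A patient with a sore trapezius could then report 0/10 and end the test. This reading is plausible and reduces the problem, so it would be wrong to say that such patients cannot meet the rule. It does not remove the problem: the later ratings are called only pain scores, no baseline helps the patient tell the two pains apart, and a long evoked sensation still has no limit.

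A second reply is that a ceiling and its scoring belong in a procedure manual or analysis plan that is not shown. That would answer a complaint about missing detail. Here the article states an end rule, and that rule as stated can fail to end.

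A reader might also infer that TS and CPM testing must wait for this test, or that all pre/post differences are disturbed. The text does not support this. Figure 1 is not shown, the ratings could run alongside questionnaires, and neither TS nor heat CPM is shown to be exposed. Nor may one infer that a large share of patients is affected, since the documents give no prevalence.

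Finally, this is one of up to 24 predictors, and the lasso may drop it. It plays no part in the second objective, the reference values in healthy participants. Both points stand and limit the weight of the finding.

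**Conclusion.** The concern holds as a measurement-design point. The stated end rule suits participants who start without pain and works badly for eligible patients with resting pain at the trapezius or with very long after-sensation. In them, a time-to-zero or whole-curve score would be arbitrary or missing, and the score would not be comparable between the healthy and patient cohorts.

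The number affected is unknown. On the assumed range of 5% to 30% it is about 3 to 16 of 54 patients in each cohort, so at least one case is very likely even at the low end. The conclusion assumes that some eligible patients have pain at the site and that the predictor is more than the first post-release score; the test's name and end rule suggest the latter, but the article does not say so. The effect on the overall model is probably modest. The change is worth making because it is cheap and protects the comparison between cohorts.

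**What to change.** In the Pain Persistence section:

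- Take one 0–10 rating at the right upper trapezius immediately before the tonic pressure.
- State that the later ratings concern pain above that baseline.
- End the ratings after two consecutive scores at or below baseline, or at a prespecified maximum number of ratings, whichever comes first.
- Score persistence over that fixed window, and record participants who reach the maximum at the cap, not as missing.

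The cost is one extra rating and a change of wording. The downside is that very long persistence is capped, so participants beyond the limit can no longer be told apart.

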#### Physiological Measurements

##### Blood Pressure

The cardiovascular system and the descending inhibitory pathways of pain appear to be closely related (48, 75). Blood pressure will be measured three times (at rest, before, and after the conditioning stimulus—see below) using a digital sphygmomanometer.

##### Blood Concentration

**Catecholamines** (53) (adrenaline, noradrenaline, dopamine, serotonin, and their metabolites), **Endocannabinoids** (anandamide, N-olcoylethanilamine, palmitoylethanolamine), and **Peptides** (83, 84) (Leu-Enképhaline, B-Endorphin, Dynorphine A, Substance P). Blood samples will be collected in K2-EDTA tubes and will be placed directly on ice. After centrifugation (4°C, 1,500 g, 15 min), samples will be directly stored at −80°C before analysis. The different analytes will be separated and analyzed by liquid chromatography coupled to a tandem mass spectrometer. The analysis will be carried out at the bioanalysis platform of the Sherbrooke Pharmacology Institute.

### Dependent Variables

#### CPM and TS Amplitude

The amplitude of CPM and TS will be assessed within a single experimental procedure, developed by Tousignant-Laflamme (85) and in accordance with Yarnitsky (18, 86). This procedure consists of a Test Stimulus applied before and after a Conditioning Stimulus (CS); the amplitude of TS is measured as the changes in pain levels observed throughout the first administration of the Test Stimulus, and the amplitude of CPM is measured as the difference in pain levels elicited by the Test Stimulus before and after the CS. This method is commonly used to measure these mechanisms (35, 55, 87, 88).

#### Pain Perception

Pain perception will be assessed using a Computerized Visual Analog Scale (CoVAS). This tool, highly validated and commonly used in research (89–91), consists of a slider placed along a visual analog scale (left end: 0, or no pain; right end: 100, or worst pain imaginable), linked to a computer. Participants move the slider along the scale according to their pain levels, such that their perceived pain intensity is continuously recorded by the computer.

